#### Cohort study among partners of cancer survivors

Reason of non-response before baseline (from the answer card) and during the follow-up period will be tabulated to get a better understanding of the representativeness of our sample. The distribution of baseline values of primary and secondary outcomes and additional variables will be described. The longitudinal nature of the data enables examination of the course of primary and secondary outcome measures over time in partners, using GEE for longitudinal data with time as independent variable and the outcome variables as dependent variables.

A time lag prediction model will be used to determine which characteristics predict the primary outcomes in partners of cancer survivors [48]. In this time lag model, the measurements of the predictors will be related to outcomes status 6 months later, thus relating baseline (T0) predictors to outcomes at T1, and predictors at T1 to outcomes at T2 [51]. Univariate analyses with *p* < 0.10 will be conducted, to select possible relevant predictors. Continued selection on the remaining predictors from the univariate analyses will be based on multi-collinearity and accepted in the multivariate GEE analyses if correlation coefficients are ≥ − 0.7 and ≤ 0.7 [52].

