#### Cohort study among partners of cancer survivors

In the cohort study, partners of cancer survivors (among others, partners of cancer survivors who participate in the aforementioned RCT) will be recruited. All included partners will be asked to complete questionnaires regarding their work and health at baseline (T0), and at six (T1) and 12 months (T2) follow-up.

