### Participants and recruitment

#### RCT among cancer survivors

Cancer survivors of working age (18–63 years at time of diagnosis), with histologically confirmed cancer and a life expectancy of more than 1 year will be recruited. At study entry, eligible cancer survivors have a fixed or temporary employment contract, with at least 6 months left of their contract, and a history of paid work for at least 1 year prior to diagnosis (with ≥8 contracted working hours per week). Cancer survivors can both be at work or (partly) on sick leave when entering the study. Cancer survivors will be recruited 3–18 months post-diagnosis. The cut-off for the maximum time post-diagnosis was set at 18 months for cancer survivors to be able to complete the intervention (with a maximum duration of 6 months) before a potential work disability assessment. According to Dutch legislation, work disability assessments take place after two years of sick leave to determine whether someone is disabled for work or not and may receive work disability benefits or not. Regardless of the outcome of the work disability assessment, employers are allowed to terminate the employment contract after 2 years of sick leave. Moreover, cancer survivors will be eligible for participation in STEPS if they are, or have been, treated with at least radiotherapy and/or chemotherapy. Previous research has shown that cancer survivors who received complex treatments, i.e., chemotherapy, radiotherapy, or a combination thereof, indicated lower work ability than cancer survivors who were treated with surgery alone [22]. Cancer survivors with additional treatment modalities, besides radiotherapy and/or chemotherapy, will be eligible for participation as well.

Cancer survivors will be excluded if their treating physicians consider work unfeasible, if cancer survivors have serious cognitive or psychiatric problems, or other comorbidities that would preclude them from participating in the intervention program, and/or if cancer survivors lack basic proficiency in Dutch. Cancer survivors participating in concurrent studies or rehabilitation programs aimed at sustained employment, or cancer survivors who refuse the involvement of their employer in the STEPS intervention will also be excluded.

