#### Cohort study among partners of cancer survivors

Partners are defined as being married to or cohabiting with a cancer survivor who participates in the aforementioned RCT. Cancer survivors and partners of survivors will be recruited independently of each other (and will not be jointly analysed). This means that both partners of cancer survivors who do and do not participate in the RCT will be eligible to participate in the cohort study. Partners of cancer survivors who have had a cancer diagnosis no more than 24 months ago and who have a life expectancy of at least 1 year, are eligible. Partners should be registered at the same address as the cancer survivor at least 1 year pre-diagnosis. Moreover, eligible partners should be between 18 and 65 years of age, have a fixed or a temporary employment contract at the time of diagnosis of the cancer survivors, and a history of paid work for at least 1 year prior to diagnosis (with ≥8 contracted working hours per week). Partners of cancer survivors can both be at work or (partly) on sick leave when entering the study. Partners will be excluded in case of self-reported serious cognitive or psychiatric problems that would prevent them from completing the questionnaires, and/or in case they are unable to understand and complete questionnaires in Dutch.

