#### Cohort study among partners of cancer survivors

Partners of cancer survivors will be invited to participate in the cohort study through the cancer survivors who received an information package regarding the RCT. An invitation letter, information brochure, informed consent form, screening questionnaire and non-response answer card will be included in a separate package, which the cancer survivor (if applicable) may hand over to his/her partner. Partners will be asked to take a legally mandatory reflection period of at least 1 week before agreeing to participate. If a partner is interested, (s) he is asked to sign the informed consent form and complete the screening questionnaire, based on which eligibility will be checked. Upon request partners are given the opportunity to ask questions about the study in a telephone call. Partners who are not interested in participating can complete a short non-response answer card on which they can indicate their reasons of non-response.

Additional recruitment pathways (similar to the one for cancer survivors described above) consist of social media and e-mail messages through NFK, Kanker.nl, and IPSO walk-in centres.

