## Discussion

In this paper, the rationale for the STEPS study has been described consisting of: 1) a multi-centre RCT to assess the (cost-)effectiveness of the STEPS intervention, a multidisciplinary, Stages of Change-based intervention combining occupational therapy and reintegration consultation to support RTW and work retention in cancer survivors, and 2) a prospective cohort study to assess work- and health-related outcomes in partners of cancer survivors and to study which factors predict these outcomes. Regarding the RCT, it is hypothesised that the STEPS intervention, compared to usual care, will be cost-effective and effective regarding the primary and secondary health and work-related outcome measures. The extra costs of the STEPS program likely outweigh against the gains in reduced productivity loss. If proven to be (cost-)effective, the STEPS intervention will be a valuable addition to standard care for cancer survivors, which currently varies greatly in the extent to which work-related issues are addressed [4]. Results from this RCT will also help to improve the work-related care of cancer survivors as it will provide insights into which elements of work-related care are effective and which elements are not. Regarding the cohort study, it is hypothesised that living with a cancer survivor will have a substantial negative impact on work- and health-related outcomes of the partners of these survivors. Moreover, factors that that predict the development of these outcomes are expected to be identified. This information can be used to better tailor support for cancer survivors’ partners.

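### The partner cohort's course model names only time as a covariate, so its average slope pools partners at different stages after diagnosis and should not be read as the impact of the diagnosis

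*Protocol article*

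**What the plan says.** Under Statistical analyses, the cohort section says that the course of primary and secondary outcomes will be examined "using GEE for longitudinal data with time as independent variable and the outcome variables as dependent variables". No other covariate is named for this model, and the origin of time is not defined.

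Under Participants and recruitment, partners are eligible if they live with a survivor "who have had a cancer diagnosis no more than 24 months ago"; no lower limit is given. Under Design and setting, they are measured "at baseline (T0), and at six (T1) and 12 months (T2) follow-up".

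Under Study procedures, the main route is described as follows: "Partners of cancer survivors will be invited to participate in the cohort study through the cancer survivors who received an information package regarding the RCT". For those survivors the RCT criteria state: "Cancer survivors will be recruited 3–18 months post-diagnosis". Social media and e-mail messages are additional routes.

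Table 1 lists time of diagnosis among the additional variables for partners, and Table 2 notes that time since diagnosis can be derived from it. The Measurements section assigns the partners' additional variables to sample description and the prediction model; it does not mention the course model. The Discussion hypothesises that "living with a cancer survivor will have a substantial negative impact on work- and health-related outcomes of the partners".

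**The concern.** T0 is not a common point in the illness. The eligibility window of 24 months is twice the 12 months of follow-up. At the extremes, one partner contributes months 0-12 after diagnosis and another months 24-36, yet both feed the same T0-T2 contrast. Working hours, quality of life and caregiver burden may be moving in opposite directions in those two periods.

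Describing partners' work and health outcomes is one of the study's two aims. If the pooled slope is near zero, or positive, a reader looking for the hypothesised negative impact could take it as evidence against one. A worsening among recent entrants may simply have been offset by recovery among later entrants.

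**Working it through.** **The plan's own figure.** The only cohort figure is the sample size, and it reproduces: 10 variables x 10 observations = 100 in the smaller group; 100/0.5 = 200; 200/0.75 = 266.7, rounded up to 267. It is not in dispute.

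**Inputs from the article.** Entry up to 24 months after diagnosis; waves at 0, 6 and 12 months after entry; main route about 3-18 months.

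**Assumptions.** The article gives no trajectory for partners. Let f(t) be the change in weekly hours from the pre-diagnosis level, t months after diagnosis. Hours fall linearly to -4 h at month 12, then recover linearly to 0 at month 36:
- f(t) = -t/3 for t up to 12
- f(t) = -4 + (t - 12)/6 for t from 12 to 36

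Entry time s is uniform over 0-24 months.

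**Formula.** The wave contrast is the mean over s of f(s + 12) - f(s). Within each 6-month entry band f is linear, so the band mean is the value at the midpoint.

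| Entry (months) | Mean at T0 | Mean at T2 | Change |
|---|---|---|---|
| 0-6 | f(3) = -1.0 | f(15) = -3.5 | -2.5 |
| 6-12 | f(9) = -3.0 | f(21) = -2.5 | +0.5 |
| 12-18 | f(15) = -3.5 | f(27) = -1.5 | +2.0 |
| 18-24 | f(21) = -2.5 | f(33) = -0.5 | +2.0 |
| All | -2.5 | -2.0 | +0.5 |

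Overall: (-2.5 + 0.5 + 2.0 + 2.0)/4 = +0.5 h.

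**Entry over 3-18 months.** Partners entering at 3-6 months change by f(16.5) - f(4.5) = -3.25 - (-1.5) = -1.75. The overall change is (3 x -1.75 + 6 x 0.5 + 6 x 2.0)/15 = +0.65 h. The narrower window still mixes opposite signs.

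**Other assumed paths, entry uniform over 0-24 months.**
- Lowest (-4 h) at month 6, recovered by month 30: means at T0, T1 and T2 are -2.375, -2.0 and -1.125, a change of +1.25 h (+1.75 h with entry over 3-18 months). Hours rise during follow-up, but every wave lies below the pre-diagnosis level.
- Steady fall to -4 h at month 24, then flat: -2.0 at T0 and -3.5 at T2, a change of -1.5 h. This is -2.0 h for entry in months 0-12 and -1.0 h for entry in months 12-24, so the direction is preserved.

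**The case against.** Several stronger readings are tempting, and the article does not support them.

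- **The plan fixes study wave as its only time scale.** The text says only time. Wave is the natural reading, since the cohort's measurements and its time-lag model are both set out in T0, T1 and T2. It is still an inference, and a fuller analysis plan could define time otherwise.
- **The model is wrong, or turns a real loss into a gain.** Where the assumed path recovers, hours do rise during follow-up, and the wave contrast estimates that average change correctly. The three paths above are three different truths, so their spread is not an error range. What stands is cancellation within one path and dependence on enrolment timing. Both need a fall followed by recovery.
- **A flat slope would be reported as no impact.** The article does not say that the slope tests the Discussion's hypothesis. Baseline levels are also described, and actual hours as a percentage of contract hours would show a shortfall at T0. That measure uses contract hours at study entry, however, so it misses contract cuts made before entry.
- **Time since diagnosis must replace wave, and must be forced into the prediction model.** A curve on time since diagnosis mixes within-partner change with differences between early and late enrolers, and the main route gives little data before month 3. The prediction model can already include the variable; whether to force it in is a matter of preference.

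The main route also makes 0-24 months an outer range rather than the expected one. As shown, this narrows the spread of entry times without removing the mixing.

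**Conclusion.** The point holds in a limited form. As written, the course model yields a valid average change over the 12 months of follow-up, but that average depends on the mix of entry times. Under the month-12 path the same trajectory gives -2.5 h if all partners enter in the first 6 months, +2.0 h if all enter after month 18, and +0.5 h with uniform entry. These sizes rest on an assumed 4 h loss, an assumed shape and assumed uniform entry; the documents supply none of them. With a steady decline the slope keeps its sign. The slope should therefore not be interpreted as the effect of the diagnosis on partners. This concerns one descriptive analysis in the cohort. It is a cheap improvement rather than a flaw that invalidates the plan, and the randomised comparison is untouched.

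**What to change.** In the cohort part of Statistical analyses, state that time in the course model means study wave. Keep wave, add time since the survivor's diagnosis at entry and its interaction with wave, and report the course by entry period (for example 6-month bands). A curve plotted against time since diagnosis can be a supplementary display. Add a sentence that the overall wave effect describes change during follow-up, not the impact of the diagnosis.

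The cost is wording and a few parameters; time of diagnosis is already asked of partners. Estimates per period will be less precise. With 200 partners followed and four equal bands, each holds 200/4 = 50, so at the same variability its standard error is about twice the overall one (square root of 4). Fewer or wider bands would soften this.

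The change separates decline from recovery. It does not supply pre-diagnosis hours, so it cannot by itself give the size of the loss.

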**Conclusion:**

Compared to usual care, the STEPS intervention is hypothesized to be (cost-)effective and the intervention could be a valuable addition to standard care helping cancer survivors to sustain employment. Further, it is expected that living with a cancer survivor has a substantial impact on work and health of partners, while specific groups of partners that are at particular risk for this impact are likely to be identified.

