#### Cohort study among partners of cancer survivors

The primary outcomes for partners are working hours per week and health-related quality of life. Secondary outcomes include change in working hours (as a percentage of the contract hours at baseline), ‘employment status’ (at work/not at work), sick leave, health-related work functioning, caregiver burden and depression. Information on a number of additional parameters (see Table 1 for a full overview) will be gathered to describe the study sample and/or as predictors in the prediction model.

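### The partner time-lag model predicts the level of hours or SF-12 six months later without the starting value, so it supports statements about later status but not about development or impact

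*Protocol article*

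**What the plan says.** The cohort part of Statistical analyses builds the prediction model in steps. First the lag: "In this time lag model, the measurements of the predictors will be related to outcomes status 6 months later". Characteristics recorded at T0 are paired with the T1 outcome, and those recorded at T1 with the T2 outcome. Then the screen: "Univariate analyses with *p* < 0.10 will be conducted, to select possible relevant predictors". Then a correlation rule: "Continued selection on the remaining predictors from the univariate analyses will be based on multi-collinearity", with limits of -0.7 and 0.7, before the multivariate GEE. The model is for the primary partner outcomes, which the Measurements section gives as weekly working hours and health-related quality of life (SF-12).

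The candidate predictors are the additional parameters, collected "to describe the study sample and/or as predictors in the prediction model". Table 1 codes partners' hours and quality of life as primary outcomes, not as additional variables, and schedules both at T0, T1 and T2.

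The only other longitudinal cohort analysis is a GEE with time as its independent variable. In the RCT, by contrast, the GEE is stated to be adjusted for the baseline value of the outcome.

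Two places describe what the prediction result will show. The Discussion says that "factors that that predict the development of these outcomes are expected to be identified". The abstract's Conclusion says that "specific groups of partners that are at particular risk for this impact are likely to be identified".

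**The concern.** Development and impact are about movement; the specified model is about level. Gender, children at home, breadwinner status and income plausibly go with usual hours, and comorbidity and fatigue with SF-12, whether or not anything changes during follow-up. Without the starting value, such a characteristic can be significant at six months simply because the groups already differed at baseline. A group that starts higher and loses more can be missed for the same reason. The p < 0.10 screen uses the same comparison, so it also governs which variables reach the multivariable model. No other planned cohort analysis links a characteristic to change: the time-only GEE does not, and the percentage-of-contract-hours outcome is secondary and outside the prediction model. The Discussion intends the result to help tailor support for partners.

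**Working it through.** **The plan's own figure.** 10 observations × 10 variables / 0.50 = 200 partners; 200 / (1 − 0.25) = 266.7, so 267. Both reproduce. No stated figure is wrong; the point is one of specification and interpretation.

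**Inputs.** From the documents: n = 200 analysable, two lag intervals, two-sided 0.05, screen at 0.10. Assumed: SD 13 h (borrowed from the survivors' sample size calculation), six-month correlation ρ of 0.7 to 0.9, a fixed binary characteristic with 100 partners per group, and a standing gap of 4 h. Two data models were used, because the documents do not settle which applies: a stable trait plus occasion noise (the gap persists), and an autoregressive process (later values depend only on the earlier value).

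**Expected coefficient when the characteristic has no effect on development (ρ = 0.8, gap 4 h).**
- As written: stable trait 4 h; autoregressive 4 × (0.8 + 0.64)/2 = 2.88 h.
- Starting value as covariate: stable trait 4 × (1 − 0.8) = 0.8 h; autoregressive 0.
- Six-month change: stable trait 0; autoregressive −4 × (1 − 0.64)/2 = −0.72 h.

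**Rejection rate as written.** Each partner contributes two outcomes, so SE = √[13² × (1 + ρ)/2 × 2/100]. At ρ = 0.8 this is √(169 × 0.9 × 0.02) = 1.744 h.
- Stable trait: 4/1.744 = 2.29; Φ(2.29 − 1.96) = 63%.
- Autoregressive: 2.88/1.744 = 1.65; Φ(1.65 − 1.96) = 38%.
- Passing the 0.10 screen: Φ(2.29 − 1.645) = 74% and Φ(1.65 − 1.645) = 50%.

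**Simulation over ρ = 0.7 to 0.9** (stacked intervals, independence GEE, robust SE), share significant at 0.05, 4 h gap:

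| Data model | As written | Starting value as covariate | Six-month change |
|---|---|---|---|
| Stable trait plus noise | 62–65% | 15–34% | about 5% |
| Autoregressive | 29–50% | 5–7% | 11–20% |

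With no standing gap, the model as written rejects in about 5% to 6%, so the excess comes from the difference in level. For stable-trait data it is about 20% at a 2 h gap and over 99% at 8 h.

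**A real differential loss.** Suppose a group starts 4 h higher and loses 2 h more per interval (stable-trait data). The difference is 4 − 2 = +2 h at T1 and 4 − 4 = 0 h at T2, so the model as written estimates (2 + 0)/2 = +1 h. It finds the loss in the right direction in under 1% of cohorts. The model with the starting value finds it in 28%, 61% and 97% at ρ = 0.7, 0.8 and 0.9; the change model in 81%, 93% and over 99%.

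**The case against.** The strongest reply is that the protocol mostly asks the question that the model answers. The abstract's Methods, the study aims at the end of the Background, the cohort sample size section, the time-lag paragraph and the closing Conclusion all speak of factors predicting the outcomes, not their change. The 50:50 split into positive and negative outcomes also fits a status target. This stands. A reader might infer that the model tests the wrong hypothesis for the cohort's stated objective; the documents do not support that. The mismatch is with the Discussion and the abstract's Conclusion only.

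A reader might also infer that six-month change must be the main dependent variable. That does not follow. Under autoregressive data the change model itself rejects in 11–20% where the model with the starting value holds about 5–7%; under stable-trait data the order reverses. Nor does change from T0 capture impact before enrolment, since partners may enter up to 24 months after the survivor's diagnosis.

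The article nowhere expressly excludes the starting value, and a condensed article leaves detail to other documents. But it sets out the dependent variable, predictor pool and selection steps, and a one-predictor screen has no room for a second covariate.

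Finally, the sizes rest on assumed inputs, and many of the listed predictors can vary over time whereas the simulated one is fixed. It cannot be said that the model would mainly pick out partners who always worked fewer hours.

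**Conclusion.** The point holds as a mismatch between the model and two interpretive statements. The time-lag model is sound for forecasting later status. It cannot by itself show which characteristics predict development, or which groups are at risk of impact, because standing differences enter the result. With 200 partners, SD 13 h, correlation 0.7 to 0.9 and a 4 h gap, a characteristic with no effect on development is called a predictor in roughly 30% to 65% of cohorts, against a nominal 5%. The direction holds in both data models and at every correlation tried; the size depends on the assumed gap and vanishes when there is none. This concerns the cohort's prediction objective, on which its sample size rests, and leaves the RCT untouched. It should be corrected.

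**What to change.** In the cohort part of Statistical analyses, force the outcome at the start of each interval (T0 value for T1, T1 value for T2) into the time-lag GEE, both when each characteristic is screened and in the multivariable model, and exempt it from selection. Base the statements on development and risk on that model. Report a GEE with six-month change as dependent variable (T1 minus T0, T2 minus T1) as a sensitivity analysis, and discuss any characteristic on which the two disagree. If the unadjusted status model is kept, describe its result only as prediction of later status.

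The cost is wording and analysis time: hours and SF-12 are already collected from partners at all three visits, and 200 and 267 do not change. The forced term uses one of the 10 planned variables, leaving nine, and fewer characteristics are likely to reach significance. Neither model recovers impact that occurred before enrolment, which the report should state.
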